### Study objectives

#### Primary outcomes

The composite primary composite outcome is time to 1) death, **2)** first-time nursing home care or, 3) paid outpatient nursing care for the first time within 90 days after the index event, whichever occurs first.

#### Secondary outcomes

Secondary outcomes are: 1) Treatment proportions for evidence-based therapies such as Stroke Unit treatment, intravenous thrombolysis, endovascular thrombectomy, hemicraniectomy; 2) Hospital transfers; 3) Mortality (Cox regression); 4) Nursing home care; 5) Costs for acute inpatient treatment, hospital transfers, rehabilitation treatment and nursing care.

#### Sample size calculation

Sample size was calculated on the assumption that the implementation of the ANNOTeM concept in the cooperating regional hospitals reduces the rate of dependency from 39% in the control period to 32% in the intervention period, i.e. a relative reduction by one fifth. The assumptions are based on the results of the TEMPiS trial [13].

Patient recruitment started in November 2017 and will run to 31 July 2020. According to the annual case numbers, at least 1820 patients per group with defined inclusion criteria are expected in the eleven cooperating regional hospitals during the intervention period. This sample size ensures a power of 80% (corresponding to a beta of 0.20) and an alpha of 5% for a two-sided test. Case size calculation was performed in nQuery Advisor 7.0.

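### The stated 80% power at 1820 per group does not follow from 39% versus 32% at two-sided 5%: those inputs need about 733 per group, and the 2.5-fold gap is not explained

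*Protocol article*

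**What the plan says.** All the planning figures stand in the protocol article under Sample size calculation. The assumed effect is that the intervention "reduces the rate of dependency from 39% in the control period to 32% in the intervention period", described as a relative reduction of one fifth. On numbers, "at least 1820 patients per group with defined inclusion criteria are expected in the eleven cooperating regional hospitals", a count taken from annual case numbers. The next sentence turns this into a power claim: "This sample size ensures a power of 80% (corresponding to a beta of 0.20) and an alpha of 5% for a two-sided test". The section closes with "Case size calculation was performed in nQuery Advisor 7.0", without naming the test.

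The section mentions no design effect, intracluster correlation, dropout allowance or multiplicity adjustment. The Primary analysis section says that effects will be evaluated in clusters and that the 5% level is adjusted for six primary and secondary tests. It connects neither statement to the sample size.

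**The concern.** Two rates, a two-sided alpha and a power fix the sample size per group up to small differences between formulas. Here the printed number is about two and a half times what the printed inputs require. Either the power is misstated or a step is missing from the description.

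The two explanations have different consequences. If patients are treated as independent, the study has power to spare, even at a stricter alpha. If the 80% is what remains after an unstated allowance for clustering, there is no reserve, and the multiplicity adjustment in the analysis section takes power well below 80%. A reader who later meets a null result cannot tell from the article which case applies, and so cannot judge how informative that result is.

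**Working it through.** **Inputs** (all from Sample size calculation): p1 = 0.39, p2 = 0.32, difference 0.07, two-sided alpha 0.05 (z = 1.960), power 0.80 (z = 0.8416), equal groups, 1820 per group.

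**1. Attempt to reproduce the plan's figure.** Two proportions, pooled variance under the null, mean rate 0.355:

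n = [1.960 × √(2 × 0.355 × 0.645) + 0.8416 × √(0.39 × 0.61 + 0.32 × 0.68)]² / 0.07²

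= [1.960 × √0.45795 + 0.8416 × √0.4555]² / 0.0049 = (1.3263 + 0.5680)² / 0.0049 = 732.4, so 733 per group.

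The figure of 1820 is not reproduced.

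**2. Power at 1820 per group, independent patients.**

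- Standard error under the null: √(0.45795/1820) = 0.01586
- Standard error under the alternative: √(0.4555/1820) = 0.01582
- Power = Φ[(0.07 − 1.960 × 0.01586)/0.01582] = Φ(2.46) = 99.3%

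**3. Could another standard calculation give 1820 at 80%?**

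| Variant | Result |
|---|---|
| Continuity correction | 761 per group |
| Unpooled variance | 730 per group |
| Arcsine | 732 per group |
| One-sided 5% | 577 per group |
| 90% power | 980 per group |
| 95% power | 1212 per group |
| Exact one-fifth reduction (39% to 31.2%) | 587 per group |
| Log-rank, HR = ln 0.68 / ln 0.61 = 0.780, Schoenfeld | 510 events; 510/(0.39 + 0.32) ≈ 718 per group |
| Same HR, Freedman | 515 events; about 725 per group |
| 1820 read as the total (910 per group) | 87.8% power |
| Alpha 0.05/6 | 1131 per group for 80% |

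None gives 1820 per group at 80% power.

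**4. Size of the gap.** 1820/732.4 = 2.485. For the sentence to be right as a calculated power, the 1820 patients would have to carry the information of about 732 independent ones.

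**5. Effect of the multiplicity adjustment.** The article names no method. Assuming Bonferroni, alpha = 0.05/6 = 0.00833 and z = 2.638.

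- Independence, 1820 per group: Φ[(0.07 − 2.638 × 0.01586)/0.01582] = Φ(1.78) = 96.2%
- Effective size 732.4 per group (80% already includes the inflation): the standard errors are 0.02501 and 0.02494, so Φ[(0.07 − 2.638 × 0.02501)/0.02494] = Φ(0.16) = 56%

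**The case against.** The best defence is that the sentence sets a floor. The 1820 is an expected count from annual case numbers, not a stated requirement, and a sample that gives 99% power does secure at least 80%. On the stated inputs, with independent patients, that is true, and the discrepancy then lies on the safe side. Patients are identified from routine insurance data and the count comes from case numbers, so no one was recruited because of an overstated requirement. But the text gives a specific power with beta 0.20 and presents it as the output of sample size software. If 1820 is only what was expected, the required number appears nowhere.

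The second defence is that a clustering allowance was applied and the article condensed it away. This is plausible. With 11 equal hospitals (1820/11 ≈ 165 patients each) and the simple parallel-cluster formula, an intracluster correlation of (2.485 − 1)/(165.5 − 1) ≈ 0.009 would close the gap. This is only an illustration: the same hospitals appear in both periods and their starts are staggered, so the formula fits loosely. The possibility means the gap may have a sound explanation. It does not make the printed inputs yield the printed power.

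A reader might infer more than the document supports:

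- **That true power is 99%, not 80%.** This holds only under independence, and the article says effects are evaluated in clusters.
- **That the analysis ignores clustering.** The article lists covariates and does not say how clusters are modelled; that detail may be in the analysis plan.
- **That the comparison with non-network hospitals is underpowered.** The sample size section makes no power claim for it.
- **That the 39% should be replaced by the observed control-period rate.** It is a planning assumption, and replacing it now would be re-planning after the fact.

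**Conclusion.** The point holds as an error in a stated planning figure. For 39% versus 32% at two-sided 5%, 80% power needs about 733 per group (761 with continuity correction), and the stated 1820 gives about 99% under independence. The unexplained factor is about 2.5, too large to be due to rounding or choice of formula.

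The document does not show which correction is right: a higher power, or a missing inflation factor. This matters most at the adjusted alpha, where the two explanations give about 96% and about 56% (both assuming Bonferroni over six tests). The finding does not show that the study is too small or that its design is invalid. It shows that the power sentence cannot stand as written.

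**What to change.** Rewrite the sample size paragraph in one of two ways, according to what was actually done:

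- If no inflation was applied: state that 733 per group are required for 80% power, that at least 1820 per group are expected, and that this gives about 99% power if patients are independent.
- If inflation was applied: state the design effect or intracluster correlation that takes 733 to 1820, and its source.

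In either case, name the test entered in the software and add the power at the multiplicity-adjusted alpha that the analysis section applies, naming the adjustment method. Under Bonferroni this is about 96% in the first case and about 56% in the second.

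No change to enrolment is proposed. The cost is a recalculation and a revised paragraph, in which the stated power may look different.

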#### Study time scale

Eligible patients who were admitted to the cooperating hospitals from November 16th 2014 to May 31st 2017 will form the control group. After an implementation period of the ANNOTeM concept, patient recruitment was started in November 2017 in the first intervention hospitals and will continue until July 2020 for primary analysis with 90 days’ follow-up (for details see Table 1). The same periods will be used for the evaluation of time trends in non-network hospitals.

**Table 1 Tab1:** Start of implementation and recruitment of patients as well as end of recruitment of the intervention hospitals in the study

Intervention hospitals	Start of implementation period	start of recruitment	end of recruitment
BER	10/04/2017	01/02/2018	07/31/2020
LUD	07/02/2017	11/16/2017	07/31/2020
NAU	07/08/2017	11/16/2017	07/31/2020
LUC	08/20/2017	11/18/2017	07/31/2020
KYR	12/11/2017	11/16/2018	07/31/2020
STR	12/23/2017	03/23/2018	07/31/2020
TEM	12/30/2017	03/30/2018	07/31/2020
RAT	10/06/2018	01/04/2019	07/31/2020
UEC	10/16/2018	01/14/2019	07/31/2020
GAR	11/12/2018	02/10/2019	07/31/2020
PRE	10/16/2018	01/14/2019	07/31/2020

An interim analysis without significance testing is planned after completion of 50% of patient follow-ups in order to inform decision makers about the progress of the scientific evaluation and options for transition into regular care; after the last follow-up is completed end of October 2020, the final analysis is expected in January 2021 (Fig. 2).

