### Comparisons

#### Comparison of control and intervention period in cooperating regional hospitals

Patients with a diagnosis of a defined acute neurological disease and admitted to the cooperating regional hospitals during the intervention period from November 2017 to July 2020 are compared with patients of the same diagnosis group during the control period from November 2014 to May 2017 before the start of the intervention.

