### Statistical analyses

#### Primary analysis

Because health insurance data will be provided anonymously, we cannot determine the effect of telemedicine consultation on an individual patient level. Rather, we will evaluate the effects of the ANNOTeM concept in clusters. The primary outcome will be analysed as the time from the index visit to the occurrence of the compound outcome as described above. Separate Cox models will be fitted for eligible patients insured at the cooperating health insurance companies, admitted and treated in both, the pre-implementation period and the intervention period. Cox models will comprise sex (m/f only), age and co-morbidity (Y/N) as covariates. Hazard rate ratios will be used to compare time-to-compound event between the two periods. All tests will be performed at a significance level of alpha = 0.05, adjusted for two-sided testing and the k = 6 tests of the primary and secondary analysis. All tests will be performed using the statistics package ‘R’ (version 3.6).

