#### Secondary analysis

The secondary analysis compares the survival rates obtained in the primary for the network clinics with the group of non-cooperating hospitals using the log-rank-test for 2 × 2 factorial designs (control vs intervention period and network vs non-network hospitals). A treatment effect will be revealed by a significant interaction in favour of the network clinics during the intervention period.

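### The fixed calendar windows give the control group slightly more winter and less summer than the intervention group, and the primary Cox model has no season term to remove the difference

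*Protocol article*

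**What the plan says.** The section Study time scale fixes the control window: "Eligible patients who were admitted to the cooperating hospitals from November 16th 2014 to May 31st 2017 will form the control group". For the intervention group it says that "patient recruitment was started in November 2017 in the first intervention hospitals and will continue until July 2020". Table 1 in the same section gives each hospital's own start of recruitment, from 16 November 2017 (LUD and NAU) to 10 February 2019 (GAR), with one common end date of 31 July 2020. The section on the comparison of control and intervention period describes a single window, "during the intervention period from November 2017 to July 2020".

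Under Primary analysis the contrast is before versus after: "Hazard rate ratios will be used to compare time-to-compound event between the two periods". The adjustment set is given in full: "Cox models will comprise sex (m/f only), age and co-morbidity (Y/N) as covariates". Season and month of admission do not appear.

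For hospitals outside the network, Study time scale adds: "The same periods will be used for the evaluation of time trends in non-network hospitals". Secondary analysis then tests period by network: "A treatment effect will be revealed by a significant interaction in favour of the network clinics during the intervention period". The limitations paragraph of the Discussion names this parallel group as the control for a possible time trend.

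**The concern.** The control window is not a whole number of years, and the intervention windows are cut at different points of the year. The mix of admission months therefore differs between the groups because of the dates alone, even if nothing else changes between 2014 and 2020. If the risk of death, first nursing home care or first paid outpatient nursing care depends on the season of admission, part of that dependence enters the period hazard ratio. None of the three listed covariates is designed to take it out. What is at stake is a small, one-directional shift in the primary estimate. Its direction depends on which season carries the higher risk.

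**Working it through.** **Inputs.** The control window, the Table 1 start dates and the common end date come from Study time scale. For the common window I take 16 November 2017, the earliest start in Table 1, to 31 July 2020. The planned effect, 39% falling to 32%, comes from Sample size calculation. The article gives no seasonal figure to reproduce, so the seasonal amplitude is my assumption. Admissions per hospital per day are assumed equal.

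**Step 1: hospital-days by season.**
- Control: 928 days in each of 11 hospitals, 928 × 11 = 10,208.
- Intervention by Table 1: sum over the 11 hospitals = 8,491.
- Intervention on the common window: 989 × 11 = 10,879.

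| | Control | Intervention, Table 1 | Intervention, common window |
|---|---|---|---|
| Dec–Feb | 271/928 = 29.2% | 2,126/8,491 = 25.0% | 271/989 = 27.4% |
| Mar–May | 276/928 = 29.7% | 2,525/8,491 = 29.7% | 276/989 = 27.9% |
| Jun–Aug | 184/928 = 19.8% | 2,235/8,491 = 26.3% | 245/989 = 24.8% |
| Sep–Nov | 197/928 = 21.2% | 1,605/8,491 = 18.9% | 197/989 = 19.9% |

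By Table 1, each of the 11 hospitals has a lower winter share than the control window (20.4% to 29.0%) and a higher summer share (24.5% to 28.7%). The gap varies. KYR's winter share is 29.0%, almost equal to control. LUD, NAU and LUC have the same 271 winter days as control, so there only the share falls.

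**Step 2: the planned effect as a hazard ratio.** Under proportional hazards, HR = ln(1 − 0.32)/ln(1 − 0.39) = 0.3857/0.4943 = 0.780, and ln HR = −0.248.

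**Step 3: spurious hazard ratio with no intervention effect.** Let the hazard by day of admission be proportional to 1 + a·cos(2π(day − 15)/365.25), which peaks in mid-January. The mean of the cosine term is 0.0991 over control days, −0.0097 over Table 1 intervention days and 0.0343 over the common window. The spurious ratio is (1 + a × intervention mean)/(1 + a × control mean).

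| Amplitude a | Peak/trough | Table 1 | Share of planned ln HR | Common window | Share of planned ln HR |
|---|---|---|---|---|---|
| 5% | 1.11 | 0.995 | 2% | 0.997 | 1% |
| 10% | 1.22 | 0.989 | 4% | 0.994 | 3% |
| 20% | 1.50 | 0.979 | 9% | 0.987 | 5% |

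Example for a = 20%, Table 1: (1 − 0.0019)/(1 + 0.0198) = 0.979, and ln(0.979)/(−0.248) is about 0.09. A negative amplitude, with summer worse, turns the shift the other way.

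**Step 4: a cruder check.** Let r be the ratio of winter risk to risk in the rest of the year. The spurious risk ratio is (1 + (r − 1) × 0.250)/(1 + (r − 1) × 0.292). For r = 1.1, 1.2, 1.3 and 1.5, applied to the 39% control rate, this is 0.16, 0.31, 0.45 and 0.71 percentage points of the planned 7. The cosine model gives 0.2 to 0.8 points over the range in Step 3.

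**Step 5: against sampling error.** With 1,820 per group, the planned rates give about 710 and 582 events. SE(ln HR) is about √(1/710 + 1/582) = 0.056. The Table 1 shift is therefore about 0.10 to 0.39 of one standard error.

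**Step 6: what remains in the period-by-network contrast.** If non-network hospitals follow the same staggered starts, a shared seasonal effect largely cancels. If they use the common window while network hospitals follow Table 1, the residual is the Table 1 ratio divided by the common-window ratio: 0.998 at a = 5% and 0.991 at a = 20%.

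**The case against.** The strongest objection is that the mechanism is assumed. The article reports no seasonal variation in this composite, which is conditional on admission with a listed neurological diagnosis. That stands, so the point has to be put conditionally. A reader might infer that the whole winter excess is counted as intervention benefit. The dates do not support that: only the difference in month mix, about 4 points of winter share and 6 to 7 points of summer share by Table 1, can reach the hazard ratio.

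A reader might also see three winters and three springs in the control window and infer a spring imbalance. By Table 1 the pooled spring share is 29.7% in both groups. Nor do all four hospitals that start in January or February 2019 miss most of that winter. Of its 90 days, RAT misses 34, UEC and PRE 44 each, and only GAR (71) misses most.

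Second, the design already has a safeguard: matched non-network hospitals over the same periods, with an interaction test. This stands in large part, since a regional seasonal effect would mostly cancel there. It does not reach the primary hazard ratio, because that comparison is secondary, and the article does not say whether the staggered starts are mirrored outside the network.

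Third, the shift is below half a standard error even at the top of the assumed range, and further covariates could be left to an analysis plan. The size is conceded. But the article does fix the covariate list, and that list leaves in an imbalance that its own dates create.

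Fourth, month of admission may not be available. Data collection methods says that the evaluating institute receives anonymised data, and the basic data it names do not include the admission date. This stands as something to confirm. Someone must know the date in order to assign patients to periods, but that need not be the institute.

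**Conclusion.** The imbalance in season is real, follows from the stated dates, and has the same direction in all 11 hospitals and under either reading of the intervention window. The primary Cox model as listed does not remove it. Its effect on the hazard ratio is conditional and small: 0.995 to 0.979 on Table 1 dates, or 0.997 to 0.987 on the common window, for an assumed amplitude of 5% to 20% with a mid-January peak and equal daily admissions per hospital. That is at most about 9% of the planned log hazard ratio. It leans towards benefit if winter admission carries higher risk and away from it if summer does. It does not threaten the study's conclusion on its own. It is a minor refinement, worth making because it costs so little.

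**What to change.** In Primary analysis, add calendar month of admission (or season, if twelve levels are too many) to sex, age and co-morbidity, as a covariate or a stratum of the Cox model. In Secondary analysis, stratify the period-by-network log-rank test in the same way, and state whether the non-network hospitals follow the staggered starts or the common window. In Data collection methods, state that the trust party supplies month of admission with the anonymised records.

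The cost is a few model terms and one coarse date field. No patients are lost. Cutting the windows to whole years would also balance the seasons, but at a price: a control window of 1 June 2015 to 31 May 2017 keeps 731 of 928 days and drops 197 (21%). The model term is the better choice.

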### Study population

#### Inclusion criteria

To determine the composite primary outcome of time to death or first-time care at home or paid care support for the first time within 90 days after the index event, we will use routine data from three cooperating health insurance companies (AOK Nordost, BARMER, TK). For this purpose, eligible study participants must (1) have continuous health insurance with one of these health insurers during the evaluation period, (2) be admitted during the intervention or control period to one of the cooperating regional hospitals, (3) have a neurological diagnosis (International Classification of Diseases (ICD)-10 main diagnosis) such as stroke (I60–64), status epilepticus or impaired level of consciousness (G41, R40), meningitis /encephalitis (A82.0–2, A85–87, G00–03, G06–09), acute spinal cord injury (S14, S24, S34, G82), (4) and be over 18 years of age of both sexes.

We had originally planned to include patients diagnosed with traumatic brain injury (S06–07) in an earliert version of the study protocoll. However, since patients with traumatic brain injury are only rarely managed by our project partners in the participating regional hospitals they are not included in the primary study population, but rather as a companion study population in a sensitivity analysis.

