### Data collection, management, and analysis

#### Data collection methods

The health insurance data for determining the defined outcomes are provided by the cooperating statutory health insurance companies (AOK Nordost, BARMER, TK) in accordance with the defined inclusion criteria. Within the framework of ANNOTeM, pseudonymised personal data of the health insurances will be transmitted in accordance with §75 Social Security Code V to a third trust party, which forwards the data in anonymised form to the evaluating institute. This forwarding has been approved by the supervisory authorities of the participating health insurance companies.

In addition to the account data for identifying the defined outcomes and costs, basic data on age and sex, insurance status and paid nursing care or nursing home care are provided at the beginning of observation.

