### Study status

The intervention started in November 2017 and results are expected in January 2021.

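### A final analysis in January 2021 leaves late intervention patients at most 63 to 94 days of claims run-out, against more than 3.3 years for every control patient, so delayed care records could bias the primary before-after hazard ratio towards benefit

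*Protocol article*

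**What the plan says.** **Outcome source.** Under Inclusion criteria, the article says of the composite that "we will use routine data from three cooperating health insurance companies (AOK Nordost, BARMER, TK"). Data collection methods repeats this: "The health insurance data for determining the defined outcomes are provided by the cooperating statutory health insurance companies". The records then pass through a trust party, which forwards them in anonymised form to the evaluating institute. The composite is time to death, first nursing-home care or "paid outpatient nursing care for the first time within 90 days after the index event, whichever occurs first" (Primary outcomes).

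**Calendar.** Sample size calculation: "Patient recruitment started in November 2017 and will run to 31 July 2020". Study time scale: "Eligible patients who were admitted to the cooperating hospitals from November 16th 2014 to May 31st 2017 will form the control group". The same section adds that "after the last follow-up is completed end of October 2020, the final analysis is expected in January 2021". Study status agrees: "The intervention started in November 2017 and results are expected in January 2021".

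**Comparison.** Primary analysis: "Hazard rate ratios will be used to compare time-to-compound event between the two periods". Non-network hospitals are analysed for the same two periods with data from the same three insurers, but the interaction test that uses them is placed under Secondary analysis.

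The article gives no extraction date, claims lag or run-out rule. Its limitations cover time trends and people who never apply for support, but not late recording.

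**The concern.** Follow-up itself is complete: each patient has a full 90 days. The issue is how long the insurers' files have had to record what happened in those days. For first nursing-home care and first paid outpatient care the article describes no source other than those files. A care event not yet on file at the data cut would be indistinguishable from no event.

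In the primary comparison the two periods differ sharply here. Control-period records are years old, while the most recent intervention-period records are two to three months old. Any delay long enough to matter removes events from the intervention period and practically none from the control period, so the error has one direction, towards benefit. Nursing-home care and nursing-care costs among the secondary outcomes are exposed in the same way. The 120-day sensitivity analysis has 30 fewer days of run-out and so cannot serve as a check.

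**Working it through.** **1. The plan's own date.** 31 July 2020 + 90 days = 29 October 2020. This reproduces the stated end of October 2020.

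**2. Time for records to arrive after day 90.** The article names only the month, so two data cuts bracket it. A cut on 31 January 2021 would leave no time for transfer and modelling if the analysis is to fall in January, so it is the generous end.

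| | Day 90 | To 31 Dec 2020 | To 31 Jan 2021 |
|---|---|---|---|
| Last intervention patient | 29 Oct 2020 | 63 days | 94 days |
| Last control patient (31 May 2017 + 90) | 29 Aug 2017 | 1,220 days | 1,251 days |

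1,220/365.25 = 3.34 years, so every control patient has more than 3.3 years. At 120 days' follow-up the last intervention patient has 33 or 64 days.

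**3. Share of intervention time with short run-out.** Days from each recruitment start in Table 1, as printed, to 31 July 2020 inclusive: BER 942, LUD 989, NAU 989, LUC 987, KYR 624, STR 862, TEM 855, RAT 575, UEC 565, GAR 538, PRE 565. The sum is 8,491 hospital-days. Equal, uniform accrual per hospital is assumed.

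| Run-out after day 90 | Cut 31 Dec 2020 | Cut 31 Jan 2021 |
|---|---|---|
| under 182 days | 1,309/8,491 = 15.4% | 968/8,491 = 11.4% |
| under 273 days | 2,310/8,491 = 27.2% | 1,969/8,491 = 23.2% |

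The control share is 0% throughout.

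**4. Care events unseen, for an assumed lag.** Assumptions: the delay from care start to record is exponential with mean m, and care starts are uniform over days 15-90. Then

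unseen fraction = mean over hospital-days and event days of exp(−(cut − event date)/m).

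Spurious reduction in points = unseen fraction × care points. Care events are assumed to make up 20 to 30 of the 39 points, because the article gives no breakdown of the composite.

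| Mean lag m | Unseen, 31 Dec | Points, 31 Dec | Unseen, 31 Jan | Points, 31 Jan |
|---|---|---|---|---|
| 30 days | 0.18% | 0.04-0.05 | 0.06% | 0.01-0.02 |
| 60 days | 1.6% | 0.3-0.5 | 0.9% | 0.2-0.3 |
| 90 days | 4.0% | 0.8-1.2 | 2.8% | 0.6-0.8 |
| 180 days | 13.2% | 2.6-4.0 | 11.1% | 2.2-3.3 |

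Example: 0.132 × 20 = 2.6 and 0.132 × 30 = 4.0. In the control period the unseen fraction at m = 180 days is 0.0002. The planned effect is 39 − 32 = 7 points.

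**5. Check with another lag shape.** Suppose instead that every record appears after one fixed delay, with events uniform over 90 days and a 31 January cut. A delay of 90 days or less loses nothing, 120 days misses 0.5% of care events, and 180 days misses 5.4%.

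**The case against.** A reader might infer that late intervention patients do have less complete records and will look better. The documents do not support that. They give no claims lag, no extraction date and no evidence of incompleteness, and they do not say how an unbooked claim is treated. The remark in the Discussion that some people never apply for support concerns need without a claim, not delay. Under a fixed lag of 90 days or less and a cut at the end of January there is no bias at all. This objection stands, and the point is therefore a conditional risk.

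A second objection is that run-out rules usually sit in the full protocol, the analysis plan or the data-management manual, which the article says was approved, and that January 2021 is only an expectation. This stands in part: such a rule may exist, and the extraction could slip. But the article states the January date twice, and if that date is kept it caps any run-out at 94 days whatever another document says. The comment concerns that stated timetable, not an omitted detail.

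Third, non-network patients share the calendar periods and the insurers, so a common lag should largely cancel in the interaction test, and it would be wrong to say that only network patients are affected. That is right for the secondary analysis. The staggered starts, from November 2017 to February 2019, weight network patients towards later dates, so cancellation may be incomplete. The primary before-after hazard ratio does not use that group. The separate analysis of death is probably less exposed, but it does not repair the composite.

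Finally, a fixed six-month run-out is not a cure if lags are long. With a mean lag of 180 days it would still leave about 30% of the last patients' care events unseen, and about 9% with a mean lag of 90 days. This stands and shapes the fix.

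**Conclusion.** The calendar asymmetry is established from the article's own dates: at most 63 to 94 days of run-out for the last intervention patients against more than 3.3 years for every control patient. Its direction, if records are delayed, is towards benefit. Whether it matters depends on a lag that the documents do not give. Under the stated assumptions (exponential delay, care starts uniform over days 15-90, equal accrual per hospital, care events 20-30 points of the 39%), the spurious reduction is negligible to small at mean lags of 1-2 months (0.5 points or less). It is modest at 3 months (0.6-1.2) and a third or more of the planned 7 points at 6 months (2.2-4.0; 2.2/7 = 31%, 4.0/7 = 57%). The plan should be changed because the remedy is cheap and the primary comparison has no protection of its own. The documents do not show that the result will be biased.

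**What to change.** In Study time scale, state the data-extraction date and a minimum claims run-out after day 90 that applies equally to both periods. Set its length from the insurers' own service-to-booking delay in the closed control period, not from a round number. Where booking dates are available, count only records booked within that run-out in both periods. This equalises the comparison even if the lag is long, which a fixed wait alone does not.

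If January 2021 must stand, either label that analysis preliminary or end the primary intervention window early enough for every included patient to meet the run-out.

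The cost is either a delay of a few months (a six-month run-out, used here only as an illustration, would put extraction at the end of April 2021) or the loss of late admissions (about 11-15% of intervention hospital-time for six months). No new patients or data source are needed.
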